### Outcome measures

The primary endpoint of the INTIPHE trial is to compare the rate of post-TIPS overt hepatic encephalopathy between patients with left or right shunt at 24 months.

The secondary endpoints include comparing the grade and duration of hepatic encephalopathy, covert HE, the rate of shunt dysfunction, the rate of variceal rebleeding, the HE free survival, the cumulative patency rate of stent and the overall survival at 24 months between two groups.

### Outcome definitions

The grade of HE was classified into covert HE (minimal HE and grade I) and overt HE (grade II to grade IV) according to the severity of manifestation (Table 3). Stroop Test (EncephalApp developed by Jasmohan Bajaj) will be used to detect the minimal HE. An off-time and on-time value >190 s will identify a patient with covert HE. Grade I to grade IV HE will be diagnosed by clinical examination. The starting time, duration, treatment, and outcome of every episode will be recorded.

**Table 3 Tab3:** WHC and clinical description of HE

WHC	ISHEN	Description
Minimal	Covert	Psychometric or neuropsychological alterations of tests exploring psychomotor speed/executive functions or neurophysiological alterations without clinical evidence of mental change
Grade I		Trivial lack of awareness Euphoria or anxiety Shortened attention span Impairment of addition or subtraction Altered sleep rhythm
Grade II	Overt	Lethargy or apathy Disorientation for time Obvious personality change Inappropriate behavior Dyspraxia Asterixis
Grade III		Somnolence to semi stupor Responsive to stimuli Confused Gross disorientation Bizarre behavior
Grade IV		Coma

HE-free survival (HEFS) is defined as the time from D0 to the first episode of HE.

Shunt dysfunction will be suspected in the condition of rebleeding and/or the maximum flow velocity within the shunt is less than 0.5 m/s or absent on color Doppler ultrasound (CDUS). Shunt will be further confirmed by portography if the shunt stenosis is greater than 50% and/or portal-systemic gradient (PSG) is beyond 15 mmHg, and TIPS revision by balloon angioplasty and additional stent-placement will be planned.

Variceal rebleeding is defined as bleeding from gastroesophageal varices confirmed by upper gastrointestinal endoscopy.

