### Inclusion and exclusion criteria

The inclusion and exclusion criteria for the INSTIPHE trial are summarized in Table 1.

**Table 1 Tab1:** Patient eligibility criteria for INSTIPHE trial

Inclusion criteria	Exclusion criteria
• Written informed consent	• Imaging confirmed portal vein thrombosis
• Aged 18–75 years old	• History of overt hepatic encephalopathy
• Clinically or histologically diagnosed HBV-related cirrhosis by clinical presentations, laboratory tests, images, and liver biopsies)	• History of TIPS or shunt surgery (including splenectomy, surgical disconnection, or shunt)
• History of GOV bleeding confirmed by endoscopy	• Serial ammonia concentration ≥ 100μmol/L
• Rebleeding of GOV after receiving non-selective β-blockers (NSBBs) combined with endoscopic therapy	• Severe liver insufficiency (total bilirubin > 51μmol/L)
• Child-Pugh A or B	• Consolidation of refractory ascites
• Imaging (CT or MRI) suggests that the left/right first branch portal vein of the intrahepatic portal can construct a shunt	• Malignancy or other serious medical illness that may reduce life expectancy
• Adequate hematological function: Neutrophils ≥1500/mm^3^, Platelets ≥50,000/mm^3^, Prothrombin Time (PT) does not exceed the upper limit of normal control for 3 seconds	• Pulmonary artery pressure > 40 mmHg, left ventricular ejection fraction < 50%, congestive heart failure or other severe cardiopulmonary diseases
• Adequate kidney function: Creatinine <150 μmol/L	• Uncontrolled systemic infection or sepsis

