### Trial assessments

The last enrolled patient will be followed up for 24 months after the start of treatment (D0). All other patients will be followed up until the final visit of the last enrolled patient. Patients will therefore be followed up for a maximum of 48 months and a minimum of 12 months following the start of treatment. All patients will be assessed by the schedule summarized in Table 2.

**Table 2 Tab2:** Trial assessment schedule

	Enrollment	Treatment			Post-TIPS follow-up					
Evaluation/examination	≤14 days before randomization	D0	D1	D2	M1	M3	M6	M12	M18	M24
Informed consent	×									
Demographics	×									
Medical History	×									
Enhanced abdominal CT	×			×		×		×		×
Ultrasound Elastography	×			×	×	×	×	×	×	×
Upper gastrointestinal endoscopy	×				×	×	×	×	×	×
Hematology^a^	×	×	×		×	×	×	×	×	×
Biochemistry^b^	×		×		×	×	×	×	×	×
Serial ammonia concentration	×		×		×	×	×	×	×	×
Tumor markers^c^	×		×		×	×	×	×	×	×
HBV-DNA	×		×		×	×	×	×	×	×
Child-Pugh	×		×		×	×	×	×	×	×
MELD^d^	×		×		×	×	×	×	×	×
ECOG^e^	×	×	×	×	×	×	×	×	×	×
HE assessment^f^	×	×	×	×	×	×	×	×	×	×
Adverse events	×	×	×	×	×	×	×	×	×	×
Survival	×	×	×	×	×	×	×	×	×	×

^a^Measurement of red blood cells, hemoglobin, white blood cells, absolute neutrophils and absolute lymphocytes,and platelets

^b^Measurement of total bilirubin, direct and indirect bilirubin, albumin, alanine aminotransferase, aspartate aminotransferase, alkaline phosphatase, glutamine transferase, urea nitrogen, serum creatinine, potassium, sodium, prothrombin time, INR, and D-dimer

^c^Measurement of AFP, CEA, and CA-199

^d^Model for End-stage Liver Disease scores

^e^Eastern Cooperative Oncology Group

^f^Measured by Stroop Test and clinical examination

Additional non-study assessments are permitted at the discretion of the treating investigator. Follow-up will be discontinued if the patient receives liver transplantation, if the patient withdraws consent, or if a physician considers it necessary for the patient to discontinue the trial from a medical perspective.

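### As worded, covert HE already present before TIPS can be scored as post-TIPS covert HE and as an early HE-free-survival event, diluting two secondary endpoints

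*Protocol article*

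**What the plan says.** All references are to the protocol article.

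- **Eligibility (Inclusion and exclusion criteria, Table 1).** The only exclusion that names HE is "History of overt hepatic encephalopathy". Current minimal or grade I HE is not listed. An ammonia limit also applies ("Serial ammonia concentration ≥ 100μmol/L" is excluded), but Study limitations says ammonia is not a valid means of diagnosing HE.
- **What counts as HE (Outcome definitions).** "The grade of HE was classified into covert HE (minimal HE and grade I) and overt HE (grade II to grade IV"). Covert HE is therefore HE.
- **How covert HE is called (Outcome definitions).** "An off-time and on-time value >190 s will identify a patient with covert HE". The value is absolute and is not compared with the patient's own pre-TIPS result. Grade I is diagnosed clinically.
- **HE-free survival (Outcome definitions).** "HE-free survival (HEFS) is defined as the time from D0 to the first episode of HE".
- **Timing (Trial assessments, Table 2).** HE is assessed at enrolment, D0, D1, D2 and then from M1 to M24. Footnote f gives the method: "Measured by Stroop Test and clinical examination".
- **Endpoints (Outcome measures).** The primary is to "compare the rate of post-TIPS overt hepatic encephalopathy between patients with left or right shunt at 24 months". On the secondary side, "The secondary endpoints include comparing the grade and duration of hepatic encephalopathy, covert HE", and HE-free survival follows in the same list.
- **Randomisation and analysis.** Stratification is by center, Child-Pugh class and ammonia level. Statistical analysis puts all data on the intention-to-treat population, supplemented by a per-protocol set. Neither section uses baseline covert HE.

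**The concern.** The trial asks whether the choice of portal branch changes HE after the shunt. Covert HE that was there before the shunt cannot depend on the branch. Yet a patient above 190 s at enrolment is eligible, is retested within two days of the procedure, and, if still above 190 s, meets the stated rule for covert HE. Because HE-free survival starts at D0 and has no grade limit, the same result can also end that patient's HE-free time at about day 0.

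Two secondary endpoints would then mix pre-TIPS prevalence with post-TIPS incidence. Event rates rise in both arms, the difference between arms shrinks, and the reported frequency of HE after TIPS is too high. The assessment that would separate old from new cases is already scheduled, but neither definition refers to it.

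**Working it through.** **1. Follow one patient through the stated rules.** Take a patient with a Stroop value above 190 s at enrolment and no history of overt HE.

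- Table 1: not excluded on HE grounds.
- Table 2: tested again at D0, D1 and D2.
- Outcome definitions: a value still above 190 s identifies covert HE, and covert HE is HE.
- HE-free survival: the clock starts at D0, and HE of any grade can stop it.
- Primary endpoint: no event, because only overt HE counts.

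No step asks whether the HE is new.

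**2. Size of the dilution (hypothetical).** The article gives no figure on this point, so there is none to reproduce.

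Inputs:
- Incident HE rates: *I*L = 16.9% and *I*R = 33.1% (Sample size calculation). They are borrowed here as any-grade incident rates, which is an assumption.
- Evaluable patients: 130/2 = 65 per arm, less the stated 10% dropout, gives 65 × 0.9 = 58.5.
- Baseline prevalence *q*: assumed from 0 to 50% and equal in both arms. Every prevalent case is assumed to become an event.

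Formulas:
- Observed rate = *q* + (1 − *q*) × *I*
- Observed difference = (1 − *q*) × (*I*R − *I*L)
- Power (binary comparison, two-sided 5%) = Φ{[Δ − 1.96·√(2p̄(1 − p̄)/n)] / √[(pL(1 − pL) + pR(1 − pR))/n]}, with p̄ the mean of the two rates

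Example at *q* = 20%: left 0.20 + 0.80 × 0.169 = 0.3352; right 0.20 + 0.80 × 0.331 = 0.4648; difference 0.1296.

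| *q* | Left | Right | Difference (points) | Risk ratio | Power, all patients (n = 58.5) | Power, free at baseline (n = 58.5 × (1 − *q*)) |
|---|---|---|---|---|---|---|
| 0 | 16.90% | 33.10% | 16.20 | 0.51 | 52.6% | 52.6% |
| 10% | 25.21% | 39.79% | 14.58 | 0.63 | 39.0% | 48.4% |
| 20% | 33.52% | 46.48% | 12.96 | 0.72 | 29.7% | 43.9% |
| 30% | 41.83% | 53.17% | 11.34 | 0.79 | 23.1% | 39.3% |
| 50% | 58.45% | 66.55% | 8.10 | 0.88 | 14.5% | 29.5% |

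Restricting to patients free of covert HE at baseline keeps the 16.2-point difference, and its power is higher in every row above zero despite the smaller n. The shrinkage factor is 1 − *q* whatever the incident rates. If only a share *r* of prevalent cases persists after D0, and the rest behave like patients free of covert HE, replace *q* by *q* × *r*: 20% prevalence with half persisting is the 10% row.

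The 52.6% in the first row is below the planned 80%. That belongs to the sample size calculation, is a separate matter, and neither supports nor weakens this point.

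**3. Chance imbalance.** With simple 1:1 allocation and 65 per arm, the standard deviation of the between-arm difference in baseline prevalence is √(2*q*(1 − *q*)/65): 7.0 points at *q* = 20% and 8.8 points at *q* = 50%. For example, 23.5% left and 16.5% right (7 points apart) gives 0.235 + 0.765 × 0.169 = 36.4% against 0.165 + 0.835 × 0.331 = 44.1%. The difference is 7.7 points instead of 13.0. The reverse imbalance gives 30.6% against 48.8%, or 18.2 points.

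**The case against.** The strongest reply is that a new-onset reading is available. Outcome definitions makes the episode the unit and has the onset and course of each one recorded, so an episode that began before D0 need not be the first one after D0. The Introduction also describes post-TIPS HE as brain dysfunction due to the procedure. This stands in part. A reader might infer that the plan does count pre-existing cases; the article never says so, and only *can be counted* is supported. But the causal description is not carried into any scoring rule, and an absolute cut-off reapplied at D0–D2 does not tell old from new.

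HE-free survival might instead be meant as overt HE only. The text does not say that: it specifies overt for the primary endpoint and not for this one.

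It can also be said that baseline-positive patients are a matter for the analysis plan. Detailed handling may well be there. The two definitions, however, are stated in the article, and the problem lies in what they say.

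On consequence, several limits stand:

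- Randomisation balances baseline covert HE in expectation, and stratification by Child-Pugh class and ammonia may reduce the chance imbalance computed above. Not stratifying on covert HE itself is no error.
- The secondary endpoints were not powered, so no stated design target is missed.
- Prevalence, any-grade incidence and persistence of every baseline case are all assumed. Entry is limited to Child-Pugh A or B, with bilirubin and ammonia limits, so prevalence could be low.
- The power figures compare proportions, whereas the plan uses log-rank and Cox methods for time-to-event outcomes.

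**Conclusion.** The point holds as a defect of wording in two secondary endpoints, covert HE and HE-free survival. Applied literally, the stated rules let covert HE that predates TIPS be scored as a post-TIPS event at about D0–D2. The result is dilution, an overstated post-TIPS incidence and exposure to chance imbalance.

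Two stronger conclusions are not supported. The primary result is not compromised: its endpoint is overt HE, and a history of overt HE is excluded. Nor is there systematic bias between arms, since prevalent cases fall equally on both in expectation.

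The size cannot be known from the article. Under the assumptions shown, a 16.2-point difference becomes about 14.6 points at 10% prevalence, 13.0 at 20% and 8.1 at 50%. If few baseline cases exist or persist, the loss is small.

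**What to change.** In Outcome definitions:

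1. Define post-TIPS covert HE as new onset: a Stroop value above the cut-off, or grade I HE, after TIPS in a patient who had neither at the last pre-TIPS assessment. State which assessment that is. Table 2 does not say whether the D0 test precedes the procedure, and only the enrolment test is certain to precede randomisation. Using the enrolment test keeps the subset strictly pre-randomisation.
2. Define any-grade HE-free survival as time from D0 to the first new HE episode, analysed in randomised patients free of covert HE at that assessment. Keep the all-randomised analysis, adjusted for baseline covert HE, as supportive.
3. Report baseline covert HE by arm.

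Limiting HE-free survival to overt HE would also remove the problem, but it would largely duplicate the primary endpoint, which Statistical analysis already treats as time-to-event.

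No visit or test is added, and eligibility and the primary endpoint stay as they are. The price is that the covert HE and any-grade HE-free-survival analyses use fewer patients and rest on a baseline-defined subset of the intention-to-treat population. Statistical analysis, which puts all data on the full population, should state this exception.

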### Adverse events and harms

All adverse events occurring after entry into the study will be recorded. The interventions and treatments were performed, if necessary.

### Provisions for post-trial care

If the disease progression will be correlated with our trial, they will receive free treatment and a certain amount of compensation.

### Auditing plan

The clinical research center of Zhongshan Hospital will audit trial conduct every 6 months, which will be independent from investigators.

### Sample size calculation

There is currently no multi-center RCT study on comparing the rate of HE between HBV-related cirrhosis patients with shunting left/right portal vein branches. The sample size was determined on the basis of three single-center study [11–13]: the rate of HE in the patients with left branch shunt was 19.4% (2 years after TIPS), 15.4% (2 years after TIPS) and 22.6% (1 year after TIPS), while the rate of HE in the patients with right branch shunt was and 43.8% (2 years after surgery), 37.5% (2 years after surgery), and 28.6% (1 year after surgery). We presume that the rate of HE after 2 years of TIPS shunting left and right branches will be 16.9% and 33.1%, respectively. Considering a power of 80% with a bilateral alpha risk of 5% and a dropout rate of 10%, we aimed to enroll 130 patients.

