## Introduction

Gastroesophageal varices (GOV) bleeding is a common and serious complication of advanced liver cirrhosis with a median survival of less than 2 years. Despite the continuous improvement of treatments, the mortality rate within 6 weeks after GOV bleeding is as high as 15–25% [1]. Multiple guidelines have pointed out that transjugular intrahepatic portosystemic shunt (TIPS) is the rescue treatment of acute variceal hemorrhage (AVB) after failure of standard therapy and an effective second-line treatment for preventing patients with high risks from rebleeding of GOV [1–4].

The safety and stability of TIPS have been greatly improved due to the improvements of related technologies and the emergence of various novel devices, but the incidence of hepatic encephalopathy (HE) after shunting (10–50%) hindered the widespread use of TIPS [5]. Post-TIPS HE is defined as a brain dysfunction caused by TIPS, it manifests as a wide spectrum of neurological or psychiatric abnormalities ranging from subclinical alterations to coma [6, 7]. None of the administration of aspartic acid/ornithine [8], lactulose [9], or albumin [10] has been proven to effectively prevent the occurrence of HE after TIPS.

On the other hand, the target portal vein branch might affect the incidence of HE after TIPS. The anatomical study suggested that the blood of the portal vein is composed of superior mesenteric venous blood rich in intestinal toxin and splenic venous blood which is relatively. The laminar flow effect may cause the majority of splenic venous blood flow to enter the left branch of the portal vein while the majority of superior mesenteric vein blood flow enters the right branch of the portal vein. An experimental study also found that the blood ammonia concentration in the right branch of the rabbit portal vein was significantly higher than that in the left branch. Some researchers observed that compared with shunting the right branch of the portal vein, the incidence of HE after shunting the left branch was significantly reduced (15.4~28.7% vs 37.5~56.0%) [11–13]. However, the current TIPS-specific stent is applied in none of the above clinical studies, the diameter of the implanted stent is not uniform, the indications for the patients receiving TIPS treatment are different, and the definition of HE after shunting is inconsistent.

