## Methods

### Study design

This study is a randomized, controlled, single-blind, multicenter superiority trial with two parallel groups, comparing the influence of shunting the left or right branch of the portal vein on post-TIPS hepatic encephalopathy in patients with HBV-related cirrhosis. A total of 130 patients will be recruited over a period of 24 months across 5 centers in China. Centers will be chosen based on their potential to recruit a high number of patients and their expertise in TIPS treatment and will receive special training with standard TIPS procedures and HE assessment. Eligible patients will be stratified 1:1 to constructing either a left or right portal vein shunt with an 8-mm Viatorr stent (Fig. 1).

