### Randomization

Eligible patients will be randomized 1:1 into shunting the left (L Group) or right (R Group) branch of the portal vein. The randomization will be stratified by center, Child-Pugh class (Child-Pugh Class A=5–6 points or Child-Pugh Class B=7–9 points), and the serial ammonia level (lower level ≤ 50 µmol/L or higher level >50 µmol/L) before TIPS. The list will be balanced by different-sized blocks and randomly alternated. The treatment assignment of each eligible patients was generated by the web-based system and was contained in opaque envelopes. This randomization procedure was performed by the coordinator, who was isolated from data collection and analysis. The data coordination center of Zhongshan Hospital will prepare the randomization. Patients and clinicians will not be blinded to the shunting branch of the portal vein in TIPS, so the investigators who perform data evaluation and analysis will not participate in the randomization and treatment.

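### The presumed HE rates of 16.9% and 33.1% need about 247 patients for 80% power; the stated total of 130 gives about 53–55% for the 24-month endpoint

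*Protocol article*

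**What the plan says.** All the inputs are printed in the protocol article. Under Sample size calculation: "We presume that the rate of HE after 2 years of TIPS shunting left and right branches will be 16.9% and 33.1%, respectively". The next sentence reads: "Considering a power of 80% with a bilateral alpha risk of 5% and a dropout rate of 10%, we aimed to enroll 130 patients". No formula or test is named there.

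Study design makes clear that 130 is the total over both arms: "A total of 130 patients will be recruited over a period of 24 months across 5 centers in China". Randomization gives equal allocation: "Eligible patients will be randomized 1:1 into shunting the left (L Group) or right (R Group) branch of the portal vein". Outcome measures sets the primary endpoint as the rate of overt HE at 24 months. Statistical analysis names chi-square or Fisher's exact tests for categorical variables and the log-rank test for time-to-event outcomes.

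**The concern.** A 16-point difference between rates near 17% and 33% is not normally detectable with 80% power in about 60 patients per arm, so the stated total looked too small for its own inputs. The sample size statement tells a reader what a non-significant primary result can exclude. If the true power at the presumed effect is well below 80%, the trial has much less ability to detect that 16.2-point difference than the article claims, and its result would be interpreted against the wrong benchmark.

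**Working it through.** **Inputs** (Sample size calculation, Study design, Randomization): left 0.169, right 0.331, difference 0.162, mean 0.250; two-sided 5% (z = 1.960); 80% power (z = 0.842); 1:1 allocation; 10% dropout; total 130.

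**1. Trying to reproduce 130.** Pooled two-proportion formula per arm:

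n = [1.960·√(2·0.25·0.75) + 0.842·√(0.169·0.831 + 0.331·0.669)]² / 0.162²

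= (1.2002 + 0.5063)² / 0.026244 = 110.97, so 111 per arm and 222 evaluable. With dropout, 222/0.9 = 246.7, so 247.

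Other standard methods, as total enrolled after 10% dropout:

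| Method | Two-sided | One-sided |
|---|---|---|
| Pooled proportions | 247 | 196 |
| Unpooled | 243 | 192 |
| Arcsine | 245 | 194 |
| Continuity-corrected | 276 | 223 |
| Log-rank, Schoenfeld | 236 | 187 |
| Log-rank, Freedman | 258 | 205 |

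The log-rank rows divide the required events by the mean event rate of 0.25. Multiplying by 1.1 instead of dividing by 0.9 changes the totals by only a few patients (247 becomes 245). No method gives 130, and the one-sided column is excluded by the stated "bilateral alpha risk of 5"% anyway.

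**2. Power of 130 for two proportions at 24 months.** Evaluable: 130 × 0.9 = 117, or 58.5 per arm.

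z = (√58.5 × 0.162 − 1.2002) / √0.36188 = 0.065, so power is 52.6%.

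With all 130 evaluable (65 per arm), z = 0.176 and power is 57.0%. Exact enumeration at 58 per arm gives 53% for chi-square and 45% for Fisher; at 65 per arm it gives 58% and 50%.

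**3. Power by log-rank, follow-up ending at 24 months.** Under proportional hazards, HR = ln(0.831)/ln(0.669) = 0.461 and |ln HR| = 0.775. Events needed for 80% power: 4(1.960 + 0.842)²/0.775² = 52.2. Events expected: 117 × 0.25 = 29.25. Then √29.25/2 × 0.775 − 1.960 = 0.137, so power is 55%. With all 130 evaluable, 32.5 events give 60%.

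**4. Power by log-rank, using later follow-up.** Assume constant hazards and follow-up spread uniformly from 24 to 48 months. Monthly hazards are 0.1851/24 = 0.00771 (left) and 0.4020/24 = 0.01675 (right). The event probability is 1 − (e^(−24λ) − e^(−48λ))/(24λ), which is 0.241 on the left and 0.449 on the right, mean 0.345. That gives about 40 events in 117 patients (power about 69%) or about 45 in 130 (about 74%).

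**5. Detectable difference.** With 16.9% on the left and 117 evaluable, a right-branch rate of 40% needs 118 evaluable for 80% power. The detectable contrast is therefore about 16.9% versus 40%, or 23 points, against the stated 16.2.

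**The case against.** The strongest reply concerns the choice of analysis. Trial assessments keeps earlier patients under observation until the last patient's final visit, up to 48 months, and Statistical analysis censors at the end of follow-up. A log-rank test on all of that follow-up would have more events, and power of about 69–74% is a fair estimate on the assumptions in step 4. This stands as a qualification, and it means that calling the trial little better than a coin flip would be too strong on that reading. It does not bring power to 80%, and the primary endpoint is fixed at 24 months. Trial assessments also gives a 12-month minimum follow-up, so the 24–48 month range is an assumption.

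The low power is also conditional on the presumed rates. At the two cited 2-year contrasts (19.4% versus 43.8%, and 15.4% versus 37.5%), 56 and 62 per arm suffice, so 117 evaluable would give roughly 80%. That is true, but those are not the rates the article says it planned on.

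Three further inferences are tempting and are not supported:

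- **That the source of 130 has been found.** The means of the two 2-year studies, 17.4% and 40.65%, give 59 per arm, and 118 × 1.1 = 129.8. But 118/0.9 = 131.1, so the match depends on the dropout convention. There are rival explanations: Freedman's 258 is 129 per arm, which could have been taken as a total, and 33.1% is close to (37.5 + 28.6)/2 = 33.05%, which suggests it was a genuine input. The document does not settle the cause.
- **That 33.1% is itself an error because it is below both 2-year right-branch rates.** It lies within the three cited rates (28.6% to 43.8%), and planning on a smaller effect than published is conservative.
- **That the Introduction contradicts the sample size section.** The Introduction reports "the incidence of HE after shunting the left branch was significantly reduced (15.4~28.7% vs 37.5~56.0"%, which differs from the rates listed later for the same three references. It gives no time point and says that HE definitions were inconsistent. Without the sources this is a question, not a demonstrated mistake, and it does not affect the arithmetic.

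**Conclusion.** The stated rates, power and total are mutually inconsistent, and this must be corrected. On the printed inputs the requirement is about 111 per arm, 222 evaluable and 247 enrolled. For the 24-month endpoint, 130 enrolled gives about 53% power for two proportions or about 55% by log-rank, and 57–60% with no dropout. These figures assume that the presumed rates are true, that 10% of patients contribute no endpoint and, for the log-rank test, that hazards are proportional. The most favourable reading examined, with all follow-up to 48 months, reaches about 69–74%. A reader might infer that a null result will be misread or that the trial cannot succeed. Neither follows: the first is speculation, and the second depends on the true effect. What is established is that the claimed 80% is not a property of this design at the effect stated.

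**What to change.** Correct Sample size calculation so that the rates, the power and the total agree, and name the test and the dropout convention used.

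- If 16.9% versus 33.1% stands, replace the 80% with the actual power, about 53–55% at 24 months. Add the difference detectable with 80% power at 117 evaluable: about 16.9% versus 40%, or 23 points.
- If the original calculation records show that other rates produced 130, print those rates, justify them and give the dropout convention. The 17.4% and 40.65% discussed above should not be adopted without such records. Trial status reports 55 patients already recruited by May 2021, so choosing rates now to fit the number would be a retrospective justification.

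The cost is a text correction with no additional patients. The downside is that either the stated power or the target effect becomes less favourable.

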### Statistical analysis

All data will be analyzed on the intention-to-treat population and are supplemented by per-protocol set analyses. The intention-to-treat population contains all patients who will undergo randomization (irrespective of whether they successfully receive TIPS), while per-protocol set analyses only include patients who successfully receive TIPS. Continuous variables will be summarized as mean ± standard deviation or the median values (ranges) and will be compared using the independent sample *t* test or one-way analysis of variance. Categorical variables will be expressed as frequencies and compared using the Chi-Square or Fisher’s exact tests. The missing data were performed with multiple imputation by using the MICE procedure. The time-to-event primary and secondary outcomes will be calculated by the Kaplan-Meier method and compared by the log-rank test (Mantel-Haenszel version). Data will be censored when any of the following events occur : liver transplantation, death, end of follow-up time. Estimates of treatment effect (with 95% CIs) were evaluated by using Cox regression models. Two-tailed *p* values <0.05 will be considered statistically significant. All statistical calculations will be performed using SPSS V.25.0 (Chicago, IL, USA).

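### 130 patients give about 53% power, not 80%, for the stated rates of 16.9% and 33.1%; those inputs need about 240 to 247 patients

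*Protocol article*

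**What the plan says.** The Sample size calculation section of the protocol article cites three single-centre studies and then fixes its assumption: "We presume that the rate of HE after 2 years of TIPS shunting left and right branches will be 16.9% and 33.1%, respectively". The next sentence gives the remaining inputs and the result: "Considering a power of 80% with a bilateral alpha risk of 5% and a dropout rate of 10%, we aimed to enroll 130 patients". It names no formula or test.

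The other design elements needed for the check are stated elsewhere in the article:

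- **Total (Study design):** "A total of 130 patients will be recruited over a period of 24 months across 5 centers in China". The abstract repeats the figure.
- **Allocation (Randomization):** "Eligible patients will be randomized 1:1 into shunting the left (L Group) or right (R Group) branch of the portal vein".
- **Significance rule (Statistical analysis):** "Two-tailed *p* values <0.05 will be considered statistically significant".
- **Endpoint (Outcome measures):** the rate of overt HE at 24 months.
- **Tests (Statistical analysis):** chi-square or Fisher's exact for categorical variables, and log-rank for time-to-event outcomes, among which it counts the primary outcome.

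**The concern.** The section prints a complete set of inputs and a result, so the result can be checked directly. A 16.2-point difference between these rates normally needs well over 200 patients at 80% power and a two-sided 5% level, so 130 looks far too small.

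The stated power describes the trial's ability to detect its own assumed effect on its primary endpoint. The Discussion says that a positive result might lead to left-branch shunting being recommended as standard in patients at high risk of HE. A negative result would be read against the same stated power. If the true power is near one half, a non-significant result says little, yet a reader relying on 80% would treat it as evidence against an effect of the branch.

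**Working it through.** **Inputs.** From Sample size calculation: p1 = 0.169, p2 = 0.331, difference d = 0.162, power 80% (z = 0.8416), two-sided 5% (z = 1.9600), dropout 10%. From Randomization: 1:1. Derived: mean rate = 0.25; p1(1−p1) + p2(1−p2) = 0.1404 + 0.2214 = 0.3619; d² = 0.02624.

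**Step 1: try to reproduce 130.**

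- Pooled variance: n per arm = [1.9600·√(2·0.25·0.75) + 0.8416·√0.3619]² / d² = (1.2002 + 0.5063)² / 0.02624 = 111.0. Total 222; 222/0.9 = 246.7, so 247 randomised.
- Unpooled variance: n per arm = (1.9600 + 0.8416)²·0.3619 / 0.02624 = 108.2. Total 216.5; 216.5/0.9 = 240.5.
- Arcsine: 109.5 per arm, 243 randomised. Continuity-corrected: 123.0 per arm, 273 randomised.
- Log-rank on 24-month events: HR = ln(0.831)/ln(0.669) = 0.4605. Schoenfeld events = 4·(1.9600 + 0.8416)² / (ln 0.4605)² = 52.2. With a mean event rate of 0.25, 52.2/0.25/0.9 = 232 randomised, or 236 if events are first rounded up to 53. Freedman's formula gives 58 events and 258 randomised.

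The figure is not reproduced: 130/247 = 53% of the pooled requirement.

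**Step 2: relax the inputs (pooled formula, divided by 0.9).**

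| Change | Randomised |
|---|---|
| One-sided 5%, 80% power | 194 |
| Two-sided 5%, 70% power | 195 |
| One-sided 5%, 70% power | 148 |

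All three contradict the text, and none reaches 130. Inflating by 1.1 instead of dividing by 0.9 hardly matters (222 × 1.1 = 244).

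**Step 3: power with 130 randomised.** Evaluable: 130 × 0.9 = 117, or 58.5 per arm.

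- Normal approximation: z = (0.162·√58.5 − 1.2002)/√0.3619 = (1.2391 − 1.2002)/0.6016 = 0.065, so power is 52.6%.
- Exact calculation with 58 and 59 patients: 53.5% for chi-square, 46.2% for Fisher's exact test.
- Log-rank to 24 months: 117 × 0.25 = 29.25 events against 53 needed; z = ½·√29.25·0.7753 − 1.9600 = 0.137, so power is 55.4%.
- No dropout (65 per arm): z = (1.3061 − 1.2002)/0.6016 = 0.176, so power is 57.0%.

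**Step 4: what 117 evaluable patients can detect.** At 58.5 per arm, 80% power is reached at about 16.9% against 40.0% (79.9%), or 11.7% against 33.1%. That is a difference of roughly 21 to 23 points, not 16.2. The expected 95% confidence interval half-width under the stated rates is 1.96·√(0.3619/58.5) = 15.4 points, almost the whole assumed difference.

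**Step 5: where 130 might come from.** Two routes land on it, and the article states neither. The plain means of the two cited 2-year studies, (19.4 + 15.4)/2 = 17.4% and (43.8 + 37.5)/2 = 40.65%, give 58.6 per arm; 117.3/0.9 = 130.3. A one-sample formula, with 33.1% as a fixed null and 16.9% as the alternative, gives 58.4; doubled and divided by 0.9 this is 129.7, but the formula does not suit a two-arm comparison. The conclusion depends on neither.

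**The case against.** The strongest counter-argument concerns the log-rank test. Statistical analysis applies it to the primary outcome with censoring at the end of follow-up, and Trial assessments allows follow-up of up to 48 months. Events after month 24 could then count. Assuming constant hazards, follow-up spread evenly over 24 to 48 months and no other censoring, the mean cumulative rates become 24.1% and 44.9%. Then 117 patients yield about 40 events and 69% power, and 130 patients about 45 events and 74%. On that basis about 168 would need to be randomised (52.2/0.345/0.9). So the 53% figure does depend on stopping at 24 months. However, Outcome measures fixes the primary endpoint at 24 months and the sample size section presumes 2-year rates, so stopping there follows the document. The extended reading also stays below 80%.

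A second point is that the intention-to-treat analysis with multiple imputation keeps all randomised patients, so the 10% need not be wholly lost. The upper bound here is 57%, with every patient fully observed.

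A third is that the origin of 130 is unknown. That is right, and no origin should be asserted as fact. The uncertainty does not rescue the statement, because the printed inputs do not give the printed result by any standard two-sample formula.

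Finally, a full protocol or analysis plan might say more. Nothing is missing here, though: the article gives all its inputs and a total that does not follow from them.

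**Conclusion.** The concern holds. For the stated rates at 24 months, 130 randomised patients give about 53% power with 10% dropout and 57% with none, against a stated 80%. The stated inputs require about 240 to 247 patients by the usual formulas, and about 232 to 273 across the log-rank (Schoenfeld) and continuity-corrected variants. The shortfall is nearly twofold, too large for rounding, choice of formula or dropout convention to explain. The result rests on 1:1 allocation, a two-sided 5% test and the 24-month endpoint, all stated in the article. Counting later events under assumed constant hazards raises power to about 69% to 74%, still short of the claim. Because the error concerns the power for the primary endpoint, it must be corrected.

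**What to change.** Correct the Sample size calculation section and leave enrolment as it is:

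- State that 130 randomised patients (117 evaluable) give about 53% power for 16.9% against 33.1% at 24 months with a two-sided 5% test.
- State that 80% power holds for a difference of about 23 points, for example 16.9% against 40.0%.
- Name the formula and the test on which the calculation rests.
- Print other rates in place of 16.9% and 33.1% only if records show that they were the ones originally used. Recruitment began in June 2019, and a larger effect chosen afterwards would restore 80% on paper only.
- Add that a non-significant primary result will be reported with its 95% confidence interval and not as absence of an effect.

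The cost is a wording change and a less favourable power statement. No extra patients are needed for the correction. Reaching 80% power for the stated rates would be a separate decision, requiring about 240 to 247 patients.
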